## Abstract

**Background:**

Against the background of increasing use of dental implants, and thus an increasing prevalence of implant-associated complications, a deeper understanding of the biomolecular mechanisms in the peri-implant tissue is needed. Peri-implant soft tissue is in direct contact with transmucosal dental implant abutments. The aim of this trial is to distinguish the biomolecular and histological interactions of various dental abutment materials with peri-implant soft tissue.

**Methods/Design:**

The study is designed as a prospective, randomized, investigator-initiated clinical pilot trial with blinded assessment. We will ultimately include 24 eligible patients who opt for implant treatment to replace a single missing posterior tooth. Three months after implantation (submerged procedure), the study begins with the second-stage surgery. Each of the 24 patients will be given three different transmucosal abutments (zirconia, lithium disilicate, titanium) consecutively. The sequence in which the three materials are used is randomized. Peri-implant crevicular fluid is sampled weekly around the respective abutment for biomolecular analyses. After one month of wearing time, the stamping press from the second-stage surgery is used to gain a narrow gingival ring biopsy around the abutment for immunohistochemical analyses. The next abutment is then inserted. The same procedure is used for all three abutments. After sampling is completed, the patients will receive a definitive crown. The primary outcome measure of the trial is biomolecular detection of specific markers in the peri-implant crevicular fluid: matrix metalloproteinase 8, interleukin- 1β, polymorphonuclear elastase, and myeloid-related protein MRP8/14 (calprotectin). Secondary outcome measures include immunohistochemical analyses and clinical parameters.

**Discussion:**

The study design will allow us to perform correlation analyses between the clinical indices with biomarkers’ expression in the interface of the transmucosal abutments and the peri-implant soft tissue. A deeper understanding of the three abutment materials’ interactions with peri-implant soft tissue will help us understand the formation mechanisms of implant-associated complications and then develop prevention strategies.

**Trial registration:**

The trial is registered at the German Clinical Trial Register and the International Clinical Trials Registry Platform by the WHO under DRKS00006555 (Registered on 27 October 2014).

## Background

The prevalence of biological implant-associated complications rises with the increasing use of dental implants. A common biological complication is peri-implant mucositis [1, 2], with a prevalence of 50 % of all dental implant sites [3]. Biological implant-associated complications usually begin in the peri-implant soft tissue. Both connective tissue and epithelium of the peri-implant soft tissue are in direct contact with transmucosal implant abutments. Thus, the interaction between the respective abutment materials with the peri-implant soft tissue may favor, counteract, or not influence at all the development of peri-implant mucositis or of unfavorable mucosal structures such as an apical shift of the barrier epithelium [4, 5]. The particular interaction between abutment materials and soft tissue is likely to be affected by the abutments’ properties, such as bacterial adhesion [6–8], surface condition [9–12] (e.g., free surface energy, roughness), and soft tissue integration ability [4, 5]. There is only low-level evidence available on the interaction between different abutment materials with peri-implant tissues [13, 14]. It has been suggested in histological studies that the abutment materials may have an influence on the stability of peri-implant tissues [4, 5, 15], although clinical studies that compared titanium to aluminum oxide abutments [16, 17] and titanium to gold-alloy abutments [18] found no significant differences in the clinical parameters. Titanium and zirconia are well-established as abutment materials. Lithium disilicate ceramic has recently been introduced as abutment material [19, 20]. Accordingly, there is a lack of studies on lithium disilicate compared with titanium and zirconia as dental implant abutment material.

The abutment’s interaction with peri-implant soft tissue can be analyzed by quantifying possible inflammation processes. The use of biomolecular analysis of the peri-implant crevicular fluid (PICF) has been established [21, 22]. For the PICF marker analyses the biomarkers matrix metalloproteinase 8 (MMP-8), interleukin-1β (IL-1ß) and polymorphonuclear elastase (PMN-elastase) proved to be reliable indicators of peri-implant inflammation [22–28]. They also play important roles in oral wound healing [29–32]. The biomarker myeloid-related protein MRP8/14 (calprotectin) has been used only rarely in PICF marker evaluations [33]. Its correlation with periodontitis has been proven by means of gingival crevicular fluid analyses [34–37]. Its release from monocytes is induced by IL-1ß [38].

Only one recently published study [39] compared the interaction of two abutment materials (titanium versus zirconia) with peri-implant tissue by means of PICF marker analyses. No such investigation is available on the biomolecular interaction of lithium disilicate ceramic. Overall, little evidence is available on the biomolecular interactions between different abutment materials and peri-implant soft tissue. The aim of this study is to analyze the interactions at the interface of peri-implant soft tissue and three dental abutment materials (zirconia, lithium disilicate, titanium). The hypothesis is that this interface differs biomolecularly and immunohistochemically depending on the specific abutment material used.

## Methods/Design

The study protocol is reported according to the Consolidated Standards of Reporting Trials (CONSORT) statement [40]. The study was designed in accordance with the following guidelines:World’s Medical Association’s Declaration of HelsinkiClinical investigation of medical devices for human subjects – Good Clinical Practice (ISO 14155:2011)Guidelines of Good Clinical Practice (2001/20/EC)

The Ethics Commission of Ulm University approved the study design on 30 July 2013 (processing number 68/13).

## Trial design

This clinical trial was designed as a prospective, randomized investigator-initiated pilot trial to be conducted in one center. In all, 24 patients are intended to participate in the study after giving informed consent. The study design was reevaluated after the first three patients had passed the endpoint of the biomolecular and histological sampling. Since the first three patients required no adjustments post-treatment, it is feasible that for the treatment of the remaining 21 patients no further adjustments will be required.

### Participants

Participants will be 24 patients with a single missing tooth in the posterior area (premolar or molar) with both adjacent teeth in situ and who choose to undergo implant replacement. Patients will be included in the study provided they:Are between 18 and 75 years of ageHave an edentulous space at least 7 mm in widthHave primary implantation or implantation after two-stage or one-stage augmentation (sinus lift or minor lateral augmentation)Have gingiva ≥ 3 mm in heightAre in need of prosthetic treatmentAre legally competent

Patients will be excluded from the study if:Extensive lateral one-stage augmentation is required (two-stage augmentation with bone block and one-stage sinus lift or minor lateral augmentation is possible)They are smokersImplant insertion using an implant template before the beginning of the study is not possibleThe edentulous space < 7 mm in width (conservation of papilla)The gingiva < 3 mm in height at the lowest pointThere is no consent given for study participationA chronic disease is presentThey are pregnantThere is evidence of alcohol or drug abuse

### Settings and locations where the data will be collected

The study is taking place at the Department of Prosthetic Dentistry, Center of Dentistry, Ulm University. Screening began in August 2013. So far, the first eight patients have received a single-tooth implant. Five of the eight have already finished the study. All patients gave informed consent. The biomolecular analyses will take place in the Department of Clinical Chemistry, Ulm University. The immunohistochemical analyses will be carried out at the Institut für Lasertechnologien in der Medizin und Messtechnik, Ulm University. Completion of the study (last patient out) is planned for mid-2016.

### Interventions

All 24 patients will have received the three abutments consecutively, each for a 1-month wearing period. The abutments are as follows: zirconia ceramic (Z) (Zenostar MO; Wieland Dental GmbH, Pforzheim, Germany; lot S13270); lithium disilicate ceramic (L) (IPS e.max Press; Ivoclar Vivadent, Schaan, Liechtenstein; lot S44695); titanium (T) (Zenotec Ti; Wieland Dental GmbH, Pforzheim, Germany; lot 20130305 4012). The sequence of the three materials is randomly assigned. The abutments are manufactured by luting hollow Z-, L-, or T-cylinders on Variobases™ (Straumann, Basel, Switzerland; lot: HE661/HK699) by means of Multilink® Hybrid Abutment cement (Ivoclar Vivadent, Schaan, Liechtenstein; lot: T10017). The abutments’ surface roughness is adjusted by polishing them to ensure conformity. The results are checked by Ra measurements of each abutment (Ra < 0.1 μm).

The examinations and specific data collection are shown in Table 1. Screening is performed before implantation to check the inclusion/exclusion criteria. Implantation is performed according to the standardized implantation procedure in the Department of Prosthetic Dentistry making use of the Straumann®-guided surgery implantation system (Straumann, Basel, Switzerland) in combination with an implantation template after three-dimensional implant planning (CoDiagnostix; Dental Wings GmbH, Chemnitz, Germany). Bone-level Straumann implants (SLActive, RC) are submerged.

**Table 1 Tab1:** Examinations and collected data

Examination type	Examination time	Collected data
Screening	Before implantation; every patient eligible for the study regardless of his/her participation in the trial	Checking of the inclusion/exclusion criteria
Implantation	Before inclusion in clinical trial	
Pretreatment examination	Before randomization	Clinical control of implant site; informed consent
Baseline: second-stage surgery and insertion of first abutment	90 ± 14 days after implantation	Tissue sampling (control punch biopsy)
		Photo documentation
		X-ray control
PICF sampling	7, 14, 21, and 28 (±1) days after insertion of the first, second, and third abutment	PICF sampling
		Plaque Index (PI)
		Gingival Index (GI)
		Probing depth (PD)
		Bleeding on probing (BOP)
Tissue sampling and insertion of second and third abutments	2–5 days after the last PICF sampling around the first, second, and third abutment	Tissue sampling (ring biopsy)

Informed consent is given during the healing period (90 ± 14 days). Inclusion in the study and randomization takes place prior to the second-stage surgery (baseline). For the second-stage surgery, a stamping press is used, with a punch biopsy serving as a histological control specimen. The first abutment (Z, L, or T) is inserted (20 Ncm) according to the randomization process. The occlusal screw hole is provisionally closed by means of a piece of dental foam and Luxatemp Inlay (DMG, Hamburg, Germany), which is light-cured. These materials are not in contact with the gingiva.

Peri-implant crevicular fluid (PICF) is sampled both buccally and lingually every week using paper strips (Periopaper; Oraflow Inc., New York, NY, USA). Before PICF sampling, supragingival plaque is carefully removed with cotton balls to eliminate the risk of plaque contamination. Cotton rolls are applied to isolate the sample from saliva. After air-drying the teeth, the paper strips are inserted into the sulcus/pocket until there is mild resistance and then left there for 30 seconds. Samples with visible blood contamination are discarded. In addition to weekly PICF sampling, clinical parameters are recorded for the implant and both adjacent teeth, including the Plaque Index (PI), Gingival Index (GI), probing depth (PD) using an electronic pressure-sensitive probe (FloridaProbe, Essen, Germany) at four sites (mesiobuccal, distobuccal, mesiolingual, distolingual), and bleeding on probing (BOP). After a 1-month wearing period, the abutment is exchanged for the next one. Before unscrewing the abutment, the stamping press from the second-stage surgery is used to gain a narrow (0.6 mm) gingival ring biopsy around the abutment for immunohistochemical analyses (Figs. 1 and 2). The same procedure as described above is repeated for the second and third abutments. After completion of the sampling for biomolecular and immunohistochemical analyses, the study is completed, and the patient receives a screw-retained lithium disilicate crown.

**Fig. 1 Fig1:**
[figure not shown]
Sampling for the immunohistochemical analyses

**Fig. 2 Fig2:**
[figure not shown]
Tissue sampling. **a** Clinical situation after applying the stamping press around the zirconia abutment. **b** After removing the gingival ring biopsy and the zirconia abutment. **c** After inserting the titanium abutment. **d** Gingival ring biopsy

The three clinical investigators collecting the data received training before the first study visit to guarantee conformity.

#### Biomolecular analyses

The paper strips collected for biomolecular analyses are frozen immediately after sampling (−80 °C) and remain frozen until assayed. For the analyses, the PICF is released from the paper strip by means of analysis buffer. The incubation takes place on an orbital shaker on ice, and separation is performed by centrifugation. The supernatant is collected into a fresh tube. To exclude erythrocyte contamination, all extracts are examined with the Combur-Test® strip (Roche Diagnostics GmbH, Mannheim, Germany).

The PICF extracts are analyzed for biomolecular detection of specific markers: MMP-8, IL-1β, PMN-elastase and MRP8/14 (calprotectin). MMP-8 is analyzed with the Fluorokin MAP Multiplex Human MMP Panel (R & D Systems GmbH, Wiesbaden, Deutschland) in the Luminex 200 System (Bio-Rad Laboratories Inc., Hercules, CA, USA). The MMP-8 activity is detected by means of gelatine-zymography. IL-1ß is measured by the Bio-Plex Cytokine Assay Kit (Bio-Rad Laboratories Inc., Hercules, CA, USA) in combination with the Luminex 200 System. PMN-elastase is measured by means of the Human Elastase ELISA Kit (HyCult Biotechnology, Uden, Netherlands) and MRP8/14 is measured with the MRP8/14 ELISA Kit (Bühlmann Laboratories AG, Schönenbuch, Switzerland). The optical density for both kits is measured at 450 nm. The sensitivities are as follows: MMP-8, 8.9 pg/ml; IL-1β, 0.2 pg/ml; PMN-elastase, 0.4 ng/ml; MRP8/14, < 0.4 μg/ml.

#### Immunohistochemical analyses

Each of the four gingival biopsies per patient (one control punch biopsy and three ring biopsies around the abutment materials) (Fig. 2d) are equally divided into quarters for the immunohistochemical analyses. The biopsy specimens are fixed immediately in 4 % neutral buffered formalin at room temperature and left there for 24 hours before embedding them in paraffin. Three micrometer thick sections are prepared prior to deparaffinization. A citrate buffer (pH 6.1; Target Retrieval Solution, Dako, Carpinteria, CA, USA) is applied. A steamer is used for antigen retrieval (20 minutes) and the slides cool off for 20 minutes. A serum blocking solution (Histostain-Plus Bulk Kit, Invitrogen®, Camarillo, CA, USA; 20 minutes) is applied. The specimens are incubated with the primary antibodies Anti-Neutrophil Elastase (over night; 4 °C; 1:500), Anti-MMP 8 (over night; room temperature; 4 μg/ml), Anti-IL 1β (over night; room temperature; 1:12.5) or Anti-MRP8 antibody (over night; 4 °C; 1:750), respectively (Abcam®, Cambridge, Great Britain), targeting the same molecules which are analyzed by the biomolecular analysis. Hydrogen peroxide 0.3 % is applied to block endogenous peroxidase (10 minutes). A secondary biotinylated antibody (Histostain-Plus Bulk Kit, Invitrogen®, Camarillo, CA, USA) is used (10 minutes). Streptavidin conjugated with horseradish peroxidase (Histostain-Plus Bulk Kit, Invitrogen®, Camarillo, CA, USA) is applied (15 minutes). An AEC chromogen (AEC Single Solution, Invitrogen®, Camarillo, CA, USA) is applied (15 minutes) for final staining. The specimens are then counterstained with hematoxylin and mounted with Aquatex (Merck, Darmstadt, Germany). Negative controls are obtained by treating the sections similarly but, instead of the primary antibodies, Tris-buffered saline (TBS) is used. The staining is performed in serial sections from each specimen (e.g., lingual quarter of the control punch biopsy).

A digital image analysis system, which consists of a light microscope Axiophot (Carl Zeiss Jena, Oberkochen, Germany) and a digital color camera ProgRes C12 plus (Jenoptik, Jena, Germany) connected to a computer equipped with PeogRes-Software, is used to obtain images of the microscopic samples (magnification 100× to 400×). Morphometric analyses are performed using the software ImageJ (National Institutes of Health, Bethesda, MD, USA) with the plugins Grid and CellCounter as previously described [41].

### Outcomes

The primary outcome measure is the biomolecular detection of specific markers (MMP-8, IL-1β, PMN-elastase, MRP8/14) in the PICF samples. Secondary outcome measures include immunohistochemical analyses and clinical parameters (PI, GI, PD, BOP).

### Sample size

The study is biometrically categorized as a pilot study because of the sample size of 24 patients. During establishment of the study design, there were no clinical results on which a biometrical sample size estimation could be based. The sample size has, therefore, been set at 24 patients. The weekly PICF sampling both buccally and lingually results in 24 PICF samples from each patient. Four histological specimens (one control punch biopsy and three ring biopsies) are to be collected from each patient.

### Randomization

Randomization is performed with a threefold crossover design. The sequence of the three abutment materials is randomly assigned, resulting in six groups (ZLT, ZTL, LZT, LTZ, TZL, TLZ) with four samples for each. The study is stratified into the two gender groups.

Randomization concealment is ensured because a clinic staff member not involved in the clinical trial performs the allocation according to a randomization list.

Any eligible patient is recorded in a screening list maintained by the clinical investigators. Once a patient has given informed consent, a patient number and randomization are requested from the staff member performing the allocation according to the randomization list. The clinical investigator enters the patient number into the patient list, which also includes the appointments of each patient. The patient number and sequence of the abutment materials are transferred into the Case Report File of the baseline visit (second-stage surgery).

### Blinding (masking)

Masking is not possible for the dentist or the patient because of the visually distinguishable abutment materials. All analyses, however, are to be done masked because of the different personnel and spatial separation.

### Statistical methods

An explorative data analysis will be performed. The data will be analyzed descriptively by means of absolute and relative frequency and medians and means, respectively, as well as measures of dispersion. The analysis of the primary and secondary outcome measures will be performed using adequate statistical tests according to the distribution patterns. Power analyses and sample size estimation will be done for similar clinical studies in the future.

## Discussion

Against the background of a high prevalence of biological peri-implant complications [3], the mechanisms of the interface between peri-implant soft tissue and transmucosal abutments are of interest. The aim of the present clinical study is to obtain a deeper understanding of the interaction mechanisms via PICF marker analyses and immunohistochemical analyses.

To date, only one recently published cross-sectional clinical study [39] has investigated the interaction of abutment materials (titanium versus zirconia) with peri-implant tissue by means of PICF marker analyses. No significant differences were found between the biomarkers’ quantity (except for leptin). The present study has only the biomarker IL-1β in common with the other clinical study. Clinical parameters were not recorded (except for the presence or absence of plaque) at the time of PICF sampling. The authors recognize the benefits of a prospective, randomized clinical trial including the collection of clinical indexes for correlation with biomarker expression [39]. Our study design met those requirements. Moreover, we included a third material, lithium disilicate ceramic, which is not as well- established as titanium and zirconia for use as abutment material. It has been shown, however, to be an increasingly relevant material for abutments [19, 20]. Titanium serves as “gold standard.”

PICF marker analyses have been established to detect peri-implant inflammation [21, 22]. For the PICF marker analyses, we use three well-established biomarkers (MMP-8, IL-1ß, PMN-elastase) and MRP8/14. To date, MRP8/14 has been used only rarely in PICF marker evaluations [33]. The combination of well-established biomarkers with a rather new one allows us to evaluate its suitability for PICF marker analyses.

The role of plaque formation must be taken into account in terms of dental materials’ interaction with peri-implant soft tissue. Plaque is associated with peri-implant mucositis [42, 43] and is correlated with elevated inflammatory markers in PICF [28, 44]. In our study, we clinically determine the PI for correlation analyses with the number of biomarkers in PICF, which has not been sufficiently investigated because of the wide range of biomarkers. The formation of biofilm on dental materials has been especially well-examined for titanium and zirconia [6–9, 45]. The results are inconsistent, however, as zirconia shows less bacterial adhesion and colonization in some studies [7, 45, 46] and no differences in others [6, 8]. In the context of plaque formation, the role of surface roughness also must be discussed. Excessive surface roughness of dental materials favors biofilm formation [11, 12] with more complex microbiota [10]. A threshold for the Ra value of abutment surfaces has been found (0.2 μm), however, below which no further significant changes occur in regard to plaque accumulation [9]. The interaction between the three abutment materials with the peri-implant soft tissue should not be biased by different surface roughness in the present study. Therefore, we adjusted the Ra values of all abutments for uniformity, as indicated in previous studies [8, 45], and well below the above-mentioned threshold.

Wound healing also influences the results of PICF marker analyses [47]. This aspect will not bias our study as the study design guarantees analogue wound healing conditions for all abutment materials. Each abutment is inserted immediately after a circular gingival biopsy is performed with a stamping press. Thus, each abutment material is circularly in contact with open wound edges, and the 1-month PICF sampling takes place during the early wound healing period for each of the three abutments. This is a clinically relevant procedure especially for the “one abutment – one time” concept, where the definitive abutment is inserted directly after implantation (direct loading) or directly after second-stage surgery (delayed loading) without removing it again [48–50].

The original biopsy material (punch biopsy from second-stage surgery) serves as histological control specimen as it has not been in contact with an abutment material so far. It will also be stained immunohistochemically to detect the four biomarkers.

Washout periods between the different abutment materials may help to exclude an influence of the preceding abutment material on the tissues. Washout periods may be performed either by wearing a “neutral” abutment for a specific time between the tested abutments or by permitting tissues to heal without an abutment and punch biopsy again before inserting the next abutment. Following discussion with biometricians, the additional punch biopsies and time on top of an already prolonged procedure were deemed ethically unjustifiable. In addition, the newly formed cells and tissue in direct contact with each abutment are most likely to be affected and are circularly removed by the stamping press. Thus, we renounced washout periods in the trial. However, an influence of the preceding abutment material on the biomolecular and immunohistochemical findings of the next abutment material cannot be fully excluded. To the author’s knowledge, there is no study which has tested this aspect yet. If our biometricians detect clear evidence of previous abutment influence (worst-case scenario) only the first abutment material (*n* = 8 for each abutment material) shall be used for analysis.

The study combines biomolecular and immunohistochemical analyses – both aiming to detect the same biomarkers – and clinical analyses. This design allows a site-specific correlation analysis between those two techniques for biomarker detection as well as clinical indices to monitor gingival health.

This study is the first randomized clinical trial to combine biomolecular, immunohistochemical, and clinical analyses to determine the environment around transmucosal abutments during wound healing in humans. Two well-established abutment materials (titanium and zirconia) are compared with a more recently introduced abutment material (lithium disilicate). A deeper understanding of abutment materials’ interactions with peri-implant soft tissue will help us comprehend the formation mechanisms of implant-associated complications and to develop prevention strategies.

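### Equal wound conditions at each abutment are not what protects the material comparison; sequence balance is, and period belongs in the analysis

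*Protocol article*

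**What the plan says.** The wound-healing paragraph of the Discussion grants that wound healing affects the PICF results and then concludes: "This aspect will not bias our study as the study design guarantees analogue wound healing conditions for all abutment materials". The supporting reason is the wound itself: "Each abutment is inserted immediately after a circular gingival biopsy is performed with a stamping press". The paragraph adds that every material meets open wound edges all round and is sampled during the early healing month. It does not name the randomised sequences as the source of protection.

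Interventions describes two situations.

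- First abutment: "For the second-stage surgery, a stamping press is used, with a punch biopsy serving as a histological control specimen". Table 1 places this 90 ± 14 days after implantation, and the implants are submerged. The Discussion says that this first specimen "serves as histological control specimen as it has not been in contact with an abutment material so far".
- Second and third abutments: before the abutment is unscrewed, "the stamping press from the second-stage surgery is used to gain a narrow (0.6 mm) gingival ring biopsy around the abutment". Table 1 times this step "2–5 days after the last PICF sampling around the first, second, and third abutment".

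Randomization assigns all six orders of the three materials, four patients to each, stratified by gender. Statistical methods describes an exploratory analysis in which outcomes are tested "using adequate statistical tests according to the distribution patterns". Period (first, second or third abutment) is neither named nor excluded.

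**The concern.** The stated premise is that the wound is analogous each time. On the article's own procedures the first placement differs from the later two in the tissue removed and in the history of the site. Since the article also says that wound healing moves the primary markers, marker levels may differ between the first and later abutments whatever the material.

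A reader who takes the premise at face value has no reason to account for period, and the only stated criterion for choosing tests is the shape of the distribution. Two things are then at stake. One is precision, because a period difference left out of the model is counted as error. The other is bias if patients or samples are lost unevenly across sequences. Interventions provides for some loss, since strips with visible blood are discarded.

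**Working it through.** **Planned counts.** Six sequences × 4 patients = 24, which agrees with the stated sample size. Each material comes first in two of the six sequences, and likewise second and third: 2 × 4 = 8 patients per material in each position. This matches the n = 8 per material that the Discussion gives for a first-abutment analysis.

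**Interval between wounds.** The last PICF sample is on day 28 ± 1 (27 to 29), and tissue sampling follows 2–5 days later. Earliest: 27 + 2 = 29 days. Latest: 29 + 5 = 34 days.

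**Model.** The article gives no size for a period effect. Assume that the first period differs from the second and third by d, in units of the within-patient SD s, that the last two are alike, and that the shift is the same for all materials. Take one value per patient and period.

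**Bias at full balance.** The unadjusted zirconia-minus-titanium (Z − T) difference carries a bias of d × (number Z-first − number T-first)/N = d × (8 − 8)/24 = 0.

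**Precision if period is ignored.** Over the six sequences the period part of a patient's Z − T difference is +d, +d, −d, −d, 0, 0. Its mean is 0 and its variance is 4d²/6 = (2/3)d². The remaining variance of the difference is 2 (in units of s²). The inflation is (2 + (2/3)d²)/2 = 1 + d²/3.

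| Assumed d | Variance factor | Interval width factor (square root) | 24 patients worth |
|---|---|---|---|
| 0.5 | 1.08 | 1.04 | 22.2 |
| 1 | 1.33 | 1.15 | 18.0 |
| 1.5 | 1.75 | 1.32 | 13.7 |

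This is the variance an analyst would estimate, and so the width of the interval reported. At exact balance the point estimate is untouched.

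**Cost of modelling period.** 24 × 3 = 72 values. Patient takes 24 parameters and material 2, leaving 46 residual degrees of freedom. Period takes 2 more, leaving 44. The variance of Z − T at full balance is 2s²/24 = 0.0833 s² with or without the period term.

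**Bias when balance is lost.** If Z-first patients drop out of the comparison, the unadjusted bias in Z − T is:

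- 1 lost: −1/23 = −0.04d
- 2 lost: −2/22 = −0.09d
- 3 lost: −3/21 = −0.14d
- 4 lost: −4/20 = −0.20d

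Gender stratification can also disturb the counts, because stratum sizes are not given. If each stratum used blocks of six (an assumption), simulation gave exactly four per sequence in only about 4–17% of lists when the stratum sizes were not multiples of six. The bias reached at most 4/24 = 0.17d. A period term removes all these additive biases.

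**The case against.** The sentence is about materials, not periods, and it says that conditions are analogous, not identical. With four patients planned per sequence, every material meets the first-abutment wound equally often, so the conclusion of no bias is substantially right for an additive effect. The same stamping press is used each time, and nothing in the article shows a different outer wound outline. If the first-abutment fallback in the Discussion were used, all comparisons would be made in the same punch wound. The trial is an exploratory pilot with no powered test. All of this stands.

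Two stronger readings are tempting, and the document supports neither.

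- A reader might infer that wound healing biases the planned comparison of materials. The balanced sequences rule this out for an additive period effect at full balance, and the article has no data showing that a period effect exists.
- A reader might infer that the analysis will ignore period. Statistical methods neither commits to that nor excludes a period term. Model terms commonly stand in an analysis plan, which is not at hand, so their absence here is not an error.

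The stated reason does not survive. Protection is credited to the similarity of the wounds, whereas the procedures show different site histories and the sequences do the protecting.

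**Conclusion.** The point holds as a wrong premise with a modest practical consequence. Wound conditions may differ between the first and later abutments. The six sequences cancel an additive difference from the material contrasts only while their balance holds, and they do not restore the precision lost if period is left out.

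The loss is 8%, 33% or 75% in the variance of a paired difference for d = 0.5, 1 or 1.5, and the bias is 0.04d to 0.20d in size if one to four patients are lost from one material's first-placement group. The value of d, the equality of the last two periods, the losses and the block size are all assumptions. The degrees of freedom apply to a linear model with one value per patient and period. A wound effect that differed by material would survive both balance and a period term, which is a reason to look at results by period. Importance is moderate.

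**What to change.** 1. In the Discussion, replace the claim of a guarantee with a statement that wound conditions may differ between the first and later abutments and are balanced across materials by the randomised sequences.
2. Include patient and period (first, second, third abutment) in the material comparisons for PICF markers, histology and clinical indices. If an analysis plan already does this, a reference to it is enough.
3. Show results by period beside the overall comparison.

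The cost is one sentence, one additional table or figure, and 2 residual degrees of freedom (46 to 44), with no rise in the variance of a material contrast at full balance. Patients, visits and samples are unchanged.
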